## Abstract

Introduction: The complications from Parkinson’s disease (PD) are directly related to decreased muscle function, balance deficits, and independence loss. Practicing aquatic exercises can minimize these symptoms and slow disease progress. Objective: To develop a Multicomponent Aquatic Training (MAT) protocol for people with PD between stages 1 and 4 of the Hoehn and Yahr scale. Methods: The protocol is for a single blind controlled clinical trial. The sample will comprise of people with PD between stages 1 and 4 in Hoehn and Yahr scale, divided into a control group and MAT group (who will participate in the MAT). Musculoskeletal function, functional mobility, and balance will be the primary outcomes of interest, assessed with an isokinetic dynamometer, the Five-Times-Sit-to-Stand test (FTSST), the Timed “Up and Go” test (TUG), the 6-m gait speed test, the Berg Balance Scale (BBS), and a force platform. Quality of life (QOL), activities of daily living (ADL), and motor aspects will be the secondary outcome measures, assessed with the Parkinson’s Disease Questionnaire (PDQ-39) and Unified Parkinson’s Disease Rating Scale (UPDRS), sections II and III. The MAT will be 12 weeks long, with two 50-min sessions per week. The outcome measures will be assessed before and after the interventions. Discussion: This study is expected to establish parameters to prescribe and monitor a MAT program for people with PD in stages 1 to 4 in the Hoehn and Yahr scale, respecting individual progress and assisting the professionals in their procedure with these people.

## 1. Introduction

Parkinson’s disease (PD) is chronic, neurodegenerative, and progressive [1]. It affects the midbrain substantia nigra, reducing the availability of dopamine and other neurotransmitters [1]. PD is the fastest-growing neurodegenerative disease in the world, as its prevalence increased from 2.5 million people in 1990 to 6.1 million in 2016 [2]. The prevalence rate in Brazil is estimated at 3.3% in people 65 years old or more, totaling at least 200,000 individuals who live with the disorder [1]. This poses a challenge to the public health system, with an increasing impact on Brazilian society [1].

PD causes motor and nonmotor impairments that interfere with the patient’s independence [3]. Its cardinal signs are bradykinesia, muscle stiffness, and tremor at rest [3]. The diagnosis requires that bradykinesia is associated with at least one of the other symptoms [3]. The Hoehn and Yahr Scale (HY) was developed to assess and classify people with PD according to the degree of incapacity and staging of the disease [4,5]. This scale has five stages verified according to the progression of the signs and symptoms, ranging from (1) unilateral disease to (5) bed- or wheelchair-ridden [4,5].

The treatment for PD is interdisciplinary [6]. Drug therapy is based on levodopa supplementation, a precursor medication of the neurotransmitter dopamine [7]. However, its continuous use has side effects and causes tolerance [7]. Physical therapy with exercises aims to preserve mobility and keep the muscles active to maintain the person’s independence and quality of life [6]. Another effect of physical exercise in PD is the increase in the brain neurotrophic factors and neurotransmitters and the decrease in neuronal degeneration in the initial stages of the disease [8]. Multicomponent physical exercise is a modality that, rather than isolated training, targets various aspects of physical function, such as cardiorespiratory fitness, muscle resistance, and balance [9,10]. It also promotes psychological and social well-being, corroborating the American College of Sports Medicine (ACSM) guidelines [9,10,11]. An additional possibility is to perform aquatic exercises (AE) [10].

AE is a resource widely used in the rehabilitation of physical function in people with PD, and has been highlighted as essential to the rehabilitation process [10]. The physical properties of water, such as resistance, hydrostatic pressure, and buoyancy, are different from those found on land [10]. Hence, AEs activate and improve motor control in a safe setting, with little risk of falls [10]. Its benefits include improved movement amplitude, balance, muscle strength, and flexibility [10]. They help control bradykinesia, optimizing overall body movements and, as a result, their activities and participation [10]. These assumptions are supported by two recent systematic reviews and meta-analyses [12,13], where it was shown that water-based exercise was more advantageous than land exercise for mobility and balance for people with PD [12,13].

Given all these characteristics, water may be a facilitating environment for people with greater motor difficulties [14,15,16]. However, most of the studies conducted in water with these populations approach the mild and moderate stages of the disease, classified between stages 1 and 3 in the HY scale [14,15,16].

The effects of aquatic programs on the more advanced stages (4 and 5), however, have not been a primary focus as it is difficult for these patients to join rehabilitation programs. Moreover, patients in stage 5 are no longer as independent as necessary to participate in a program without direct supervision. Therefore, we need strategies to attend to people in stages 1 to 4, aiming to delay the evolution of the disease and symptoms and progress into stage 5, as much as possible. Given the above, the objective of this study is to develop a Multicomponent Aquatic Training (MAT) protocol for PD patients in stages 1 to 4 on the HY scale. Sharing this protocol with the scientific community is the first step of a wider project objective to analyze the effects of MAT on the physical performance and cognitive state of people with PD.

## 2. Method

### 2.1. Study Design

This is a protocol for a single blind controlled clinical trial with two parallel groups, into which the participants will be allocated.

The MAT study protocol was developed based on the Standard Protocol Items: Recommendations for Interventional Trials (SPIRIT) [17]. The project was approved by the Ethics Committee of the Department of Health Sciences at the Federal University of Paraná, Curitiba, Paraná, Brazil (CAAE no. 66781417.4.0000.0102 and certification no. 2.200.372), and filed in the Brazilian Registry of Clinical Trials under RBR-6hnqcv. This is a Multicomponent Aquatic Training program, named MAT, to be conducted with participants with a clinical diagnosis of PD. The enrolled PD patients will be assessed at baseline (i.e., before dividing them into groups) and after three months. Any changes made in the protocol will be reported to the Research Ethics Committee and changed in the Brazilian Registry of Clinical Trials.

### 2.2. Study Setting

The study will be carried out in Curitiba, the capital of the state of Paraná, Brazil, where the Association of People with Parkinson’s Disease of Paraná (APPP) is located. The APPP is a nonprofit association founded 20 years ago, serving as a municipal, state, and federal public utility service that benefits about 1100 people with PD [18].

### 2.3. Participants

Individuals with PD residing in Curitiba or its metropolitan area will be invited to participate in the study, which will be advertised at APPP and in digital media.

The eligibility criteria for inclusion in the study are people of both sexes, diagnosed with idiopathic PD in stages 1 to 4 on the HY scale, who agree to participate in the research and sign the informed consent form (ICF), able to walk unassisted, and who have a medical certificate to perform physical exercises in a heated pool.

The exclusion criteria are diseases that cause vestibular or balance changes, or sensory, visual, or auditory deficits that hinder individuals from understanding the verbal or visual commands; absolute or relative contraindications to heated pool attendance; changes in the dosage or parameters of PD-related medication throughout the study as well as the implementation or withdrawal of Deep Brain Stimulation (DBS); change in physical activity levels during the study; being part of any other research up to three months before the first assessment of the study; not agreeing to or not signing the ICF; and withdrawing from the study.

All assessments and interventions will be carried out in the “on” period of medication for participants who meet the inclusion criteria.

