### 2.9. Separation of the Groups and Allocation Concealment

The allocation of the 2 groups will be based on patient preference. Before completing the pre-intervention assessments, the participants will be divided into two equal-sized groups. The researcher responsible for the assessment will not know which group each participant is allocated to.

The participants will be instructed not to tell the researchers who assess them which study group they are a part of. Thus, the researchers who conduct the assessments will be blinded to the allocation and size of the groups.

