### 2.14. Sample Size

A sample size calculation was used to determine the number of participants required for the present study. The calculation was based on the prevalence of PD in Curitiba, Paraná. The sample calculation was performed using GPower 3.1 software, which stipulated a minimum sample of 30 individuals, assuming an effect size of 0.25 on a probability distribution F, whose value consisted of a mean distance between the sample mean and the population mean; a Type I error equal to 0.05 and analysis power equal to 0.84. Thus, the study will require 30 individuals with PD—15 allocated in the MAT group, and 15 in the control group. However, an extra 10% of participants will be added in order to avoid possible drop outs.

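### The PD-medication stability criterion covers only the study period, so a recent change before baseline does not bar entry; the DBS clause gives no clear time frame

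*Protocol article*

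**What the plan says.** Section 2.3 lists among the exclusions "changes in the dosage or parameters of PD-related medication throughout the study as well as the implementation or withdrawal of Deep Brain Stimulation (DBS"). The time words belong to the medication half; the DBS half has none. Activity level is treated like medication, with a criterion covering the study period only: "change in physical activity levels during the study".

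The one look-back before baseline in the same list concerns something else: "being part of any other research up to three months before the first assessment of the study". The inclusion criteria require patients "diagnosed with idiopathic PD in stages 1 to 4 on the HY scale" and set no condition on how long the current regimen has been in place. Section 2.3 also states: "All assessments and interventions will be carried out in the “on” period of medication".

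Three other features bear on the point:
- Section 2.1: patients "will be assessed at baseline (i.e., before dividing them into groups) and after three months", so there is one measurement before and one after, with no run-in.
- Section 2.9: "The allocation of the 2 groups will be based on patient preference".
- Section 2.14: "15 allocated in the MAT group, and 15 in the control group". Section 2.15 then plans a mixed-model ANOVA over time and group and names no covariate for recent treatment change.

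**The concern.** The criterion recognises that a change in PD medication disturbs a before/after comparison, since such a change during the study excludes the patient. A change made just before baseline can act on the same comparison if its effect is still building up when the first measurement is taken. As written, it is not excluded.

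TUG, gait speed, the sit-to-stand test, the Berg scale and UPDRS II and III measure motor function and daily activities, which PD treatment is meant to affect. Testing in the on-medication state fixes the moment within the dose cycle. It does not show that the regimen has settled.

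With a single baseline, such drift cannot be told apart from a change due to training or to usual activity. Without randomisation, nothing in the design tends to spread recently adjusted patients evenly. At 15 per group, a few of them can move a group mean.

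**Working it through.** **What the text admits.** Take a patient whose PD drug was changed shortly before the first assessment and not changed again.
- Inclusion criteria: none refers to regimen stability, so they can be met.
- Medication exclusion: covers the study period, so it is not triggered.
- Three-month look-back: covers other research only, so it is not triggered.
- On-medication testing: can be satisfied.

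The patient is eligible. For a patient with DBS implanted shortly before baseline, the answer depends on how the clause is read. If the study-period limit carries over, the patient enters; if the clause has no time limit, the patient is excluded.

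**Effect on the comparison.** Let *a* and *b* be the numbers of affected patients in the two groups of 15, and *d* their mean drift.
- Shift in one group's mean change = *a* × *d* / 15, which does not depend on the other group.
- Shift in the group-by-time contrast = (*a* − *b*) × *d* / 15, which is zero when *a* = *b*.

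The article gives neither the number of recent changers nor the size of any drift, so both are assumptions. For an excess *a* − *b* of 1 to 3 and *d* of 0.5 to 1.5 SD:
- lowest: 1 × 0.5 / 15 = 0.03 SD
- middle: 3 × 1.0 / 15 = 0.20 SD
- highest: 3 × 1.5 / 15 = 0.30 SD

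**Against the planned effect.** Section 2.14 gives f = 0.25, alpha 0.05, power 0.84 and N = 30, without the correlation ρ between the two measurements. Power at N = 30, from the noncentral F distribution with two groups and two time points:

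| Test | Noncentrality | Power |
|---|---|---|
| Group-by-time, ρ = 0.5 | 0.0625 × 30 × 2 / 0.5 = 7.5 | 0.753 |
| Group-by-time, ρ = 0.6 | 0.0625 × 30 × 2 / 0.4 = 9.375 | 0.840 |
| Between groups, averaged over time, ρ = 0 to 0.8 | 0.0625 × 30 × 2 / (1 + ρ) | 0.464 to 0.286 |
| One-way, single time point | 0.0625 × 30 = 1.875 | 0.262 |

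The stated 30 and 0.84 are reproduced by the interaction test if ρ is about 0.6. They are not reproduced by the between-group or one-way forms. On a 2 × 2 interaction, f = 0.25 means cell effects of ±0.25 SD, so the difference between the groups' changes is 4 × 0.25 = 1.0 SD. The shift of 0.03 to 0.30 SD is then about 3% to 30% of the planned net change.

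**Effect on false positives.** Two-sample t test on change scores, 15 per group, no true effect. Here drift is in units of the SD of change, which equals the outcome SD when ρ = 0.5. The drift is added as a fixed shift and the variance is left unchanged, which is a simplification.

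| Affected, by group | Drift | Shift in contrast | Type I error |
|---|---|---|---|
| 1 v 1 | 0.5 to 1.0 | 0 | 0.050 |
| 3 v 1 | 0.5 to 1.0 | 0.07 to 0.13 | 0.054 to 0.064 |
| 4 v 1 | 0.5 to 1.0 | 0.10 to 0.20 | 0.058 to 0.083 |
| 5 v 0 | 0.5 to 1.0 | 0.17 to 0.33 | 0.073 to 0.143 |

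The last row lies outside the assumed excess of 1 to 3 and shows a more extreme split.

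**The case against.** The strongest reply is that this is an omission in a condensed article, and that a medication-history window may stand in the full protocol. That carries some weight, but the article does not leave the time frame open. It states one for medication, which stops short of baseline, while giving a look-back to a different criterion in the same list. The stated criterion is the problem.

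A second reply is that the gap is narrow: a patient still being titrated would be excluded at the next adjustment. This stands. What remains is the patient with a recent change, no further change for three months, and a response that is still developing. The article gives no sign of how many there are.

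A third reply is that common drift cancels, that modest imbalance leaves the type I error near nominal, and that preference allocation is the larger source of imbalance. All three are correct. They limit the size of the problem without removing it, and they do not protect the within-group before/after comparison.

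Some stronger readings are tempting and are not supported:
- A reader might infer that a patient given DBS just before baseline is clearly admitted. The clause has no time words, so this is one possible reading only.
- A reader might take f = 0.25 as a 0.5 SD difference between two groups and put the shift at up to 0.30 / 0.5 = 60% of the planned effect. That does not fit the planned interaction test, and between-group forms cannot reach the stated power.
- A reader might take three months as the needed stability period. The article sets it for participation in other research and does not link it to the time a treatment change takes to settle.

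**Conclusion.** The point holds for medication: the criterion starts too late for a before/after outcome, and nothing else in the article removes or balances the resulting drift. For DBS the finding is only that the wording is ambiguous.

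It would be wrong to conclude that drift necessarily passes for a training effect. The between-group contrast is biased only if recently changed patients are unevenly split, which this design does not prevent. Within-group changes are affected in any case.

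The actual size cannot be known from the article. The 30% ceiling needs the largest assumed excess and the largest assumed drift together, and rests on reading f = 0.25 as the interaction effect over two time points. The low end, 0.03 SD, is negligible. This is a possible bias of uncertain and probably moderate size that is cheap to reduce before enrolment. Correcting it afterwards would mean losing patients from a sample of about 30.

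**What to change.** In section 2.3:
- extend the PD-medication criterion to a stated period before the first assessment as well as the study itself;
- state the time frame of the DBS clause explicitly, including what applies before baseline;
- allow candidates to be re-screened once the period has passed.

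The investigators should choose the length of the period on clinical grounds. The existing look-back for other research is a precedent for the form of words, not for the duration.

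The cost is a sentence or two in the criteria, a short treatment history at the initial assessment, and the notification to the ethics committee and registry that section 2.1 already foresees for protocol changes. The drawback is that some candidates will wait before baseline, in a trial whose Discussion already names recruitment difficulty as a limitation. The change does not address the other imbalances that preference allocation can bring.

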### 2.7. Adverse Results

Adverse events will be monitored and prevented as the participants will be accompanied during their transition to the pool, throughout the exercise, and when their HR and AP are measured, always monitoring the intensity of their effort during the physical activity. During aquatic physical training, the participants will be individually accompanied by physical therapists and/or a support team inside and outside of the pool to ensure they do not perform the exercises incorrectly, thus avoiding aquatic accidents, such as momentary drownings.

In addition, the professionals will record the AP, HR, and breathing rate of participants before and after the training. In the event of any falls or incidents related to the subjects’ health status occurring during the intervention, the events will be recorded accordingly. During the training, the participants will also be monitored with the perceived exertion scale (BORG C20) to ensure they do not exceed the recommended intensity level. Participants must remain between 13 and 17, which would correspond to 66% and 80% of maximum voluntary strength production, respectively, as recommended by the American College of Sports Medicine 2014 [11]. If any musculoskeletal injuries occur, the training will be halted.

If any of the participants interrupt the protocol, follow-up data will be collected, and the adverse effects will be reported in the publication of the results. Delayed onset muscle soreness following physical training will not be considered an adverse effect as it is an expected result of the exercise. In the event of muscle soreness, participants will be referred for cryotherapy.

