### 2.8. Recruitment

The participants will be informed about the project via a phone call and then invited to participate in the initial assessment. Before beginning the assessment, they will be informed of their voluntary participation in the study and sign the informed consent form—which has been revised and approved by the Ethics Committee of the Department of Health Sciences at the Federal University of Paraná. The study will be conducted in compliance with Brazilian Resolution 466/12, which is in line with the World Medical Association Declaration of Helsinki.

Other assessments planned for the pre-intervention period will be scheduled for the participants who meet the inclusion criteria and do not meet any of the exclusion criteria, as schematized in Figure 1.

The research team will read the informed consent form together with the participant and answer any questions they might have. Once the participants are fully informed and feel sure on their participation, they will sign two copies of the document (researchers and participants). All the collected data will be stored in secure locations, identified only with the participants’ code. The data will be used for publication in scientific journals without identifying any of the participants. In addition, at the end of the study, the participants will be handed a report with the data of their initial and final assessments. The data will be published regardless of the effects of the intervention—i.e., whether they are positive or negative.

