### 2.12. Secondary Outcome Measures

Quality of life, motor function, and activities of daily living will be assessed as secondary outcome measures, as they are strongly influenced by the primary outcome measures.

Quality of life will be assessed with the Parkinson’s Disease Questionnaire (PDQ-39) [28,29]. The questionnaire has 39 questions divided into eight dimensions, namely: mobility, activities of daily living, emotional well-being, stigma (which assesses social difficulties in PD), social support, cognition, communication, and bodily discomfort [28,29]. The total score ranges from 0 to 100—the lower the score, the better the perception of health status [28,29].

Motor function and activities of daily living will be assessed with the Unified Parkinson’s Disease Rating Scale (UPDRS), sections II and III [30]. The UPDRS is an assessment scale for the patients’ signs, symptoms, and certain activities based on self-report and clinical observation [30]. It has 42 items distributed into four parts: mental activity, behavior, and mood (I); activities of daily living (II); motor examination (III); and drug therapy complications (IV) [30]. Each item scores from 0 (tending to normal) to 4 (greater impairment from the disease) [30].

Adherence and dropouts will also be collected to determine the tolerability and satisfaction of participants in the MAT.

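### Events that can only occur after entry are listed as exclusion criteria, so participants may be selected on how they fared after allocation

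*Protocol article*

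**What the plan says.** Section 2.3 (Participants) mixes two kinds of exclusion criteria. Some are baseline facts, such as vestibular disease or a contraindication to the heated pool. Others are defined over the study period: "changes in the dosage or parameters of PD-related medication throughout the study", the start or withdrawal of DBS, "change in physical activity levels during the study", "and withdrawing from the study".

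Section 2.8 (Recruitment) uses the criteria as a gate to the remaining baseline assessments, which are scheduled for "participants who meet the inclusion criteria and do not meet any of the exclusion criteria".

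Four other places bear on the point:

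- Section 2.7: "If any of the participants interrupt the protocol, follow-up data will be collected".
- Section 2.12: "Adherence and dropouts will also be collected to determine the tolerability and satisfaction of participants in the MAT".
- Section 2.9: "The allocation of the 2 groups will be based on patient preference".
- Section 2.4: participants are asked not to take up any other physical training while the study runs.

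Section 2.14 sets 30 participants (15 per group) plus 10% for dropout. Section 2.15 plans a mixed-model ANOVA of group by initial and final assessment. It says nothing that would bring excluded participants back into the comparison.

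**The concern.** An exclusion criterion should be decidable before a participant is allocated. Medication change, activity change and withdrawal during 12 weeks are not. The only workable reading is that participants who meet them later are taken out of the study.

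Those events are not neutral. A participant whose symptoms worsen is more likely to have medication adjusted. A MAT participant who tolerates the training badly is more likely to withdraw, and only the MAT group can leave because of the training. Section 2.12 itself treats dropout as a sign of how well MAT is tolerated. The final comparison would then be between those who remained eligible in each group. The direction of the bias depends on which group loses its decliners: losing them from the control group hides a benefit, and losing them from the MAT group creates one.

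With 15 per group, each removal takes 1/15 = 6.7% of a group.

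**Working it through.** **1. Can the criteria act at screening?**

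| Criterion in section 2.3 | Decidable at screening (section 2.8)? | Can it depend on group or symptom course? |
|---|---|---|
| PD medication change | No | Yes |
| DBS start or withdrawal | No, if read over the study period like the medication criterion it is joined to | Unlikely within 12 weeks |
| Activity change | No | Yes |
| Withdrawal | No | Yes |

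**2. The plan's own figure.** Section 2.14 gives effect size 0.25 on an F distribution, alpha 0.05, power 0.84 and N = 30. Reading 0.25 as Cohen's f for the group-by-time interaction with m = 2 visits:

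lambda = N × f² × m / (1 − rho), with 1 and N − 2 degrees of freedom.

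The article does not state rho. At rho = 0.6, lambda = 30 × 0.0625 × 2 / 0.4 = 9.375 and power is 0.84, as stated. At rho = 0.5 power is 0.75. I use 0.6 because it reproduces the plan. In a 2 × 2 layout f = 0.25 is a net difference in change of 4 × 0.25 = 1.0 SD.

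**3. Set-up for the illustration (assumptions, not figures from the article).** There are 15 per arm. Change scores are normal with SD √(2 × (1 − 0.6)) = 0.894. Two or three participants (13.3% or 20%) are removed from one arm only. The test is a t-test on change, which is equivalent to the interaction F. Removal is ranked on a score that correlates with change at 0.5 (partial selection) or 1 (worst case, strictly the worst changers).

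**4. Results by simulation.**

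| Scenario | Removed | Correlation 0.5 | Worst case |
|---|---|---|---|
| No effect, MAT decliners removed | 2 | +0.10 SD, 6% false positives | +0.21 SD, 11% |
| | 3 | +0.15 SD, 7.5% | +0.29 SD, 16% |
| True 1.0 SD, control decliners removed | 2 | 0.90 SD, power 0.74 | 0.80 SD, power 0.68 |
| | 3 | 0.85 SD, power 0.68 | 0.71 SD, power 0.57 |

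Reference values at a true 1.0 SD: power is 0.84 with full data and 0.79 with 3 controls removed at random. So 0.05 of the power loss at 3 removals is plain sample loss, and the rest comes from selection.

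**5. Plausibility check.** Cutting the worst 20% of a large normal sample moves its mean by 0.35 SD of change, and 0.35 × 0.894 = 0.31 SD. That is close to the simulated 0.29 for 3 of 15. The shift scales with the correlation: 0.5 × 0.29 = 0.145, which agrees with +0.15.

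**6. Room in the sample.** Ten per cent extra means 30 × 1.1 = 33, or 30 / 0.9 = 33.3, rounded up to 34. Exclusions and dropouts together can therefore reach only 3 or 4 before the sample falls below 30.

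**The case against.** Several stronger readings are tempting, and the article does not support them.

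- **A contradiction with section 2.7.** A reader might infer that following up those who interrupt is incompatible with excluding those who withdraw. Interrupting the protocol is not the same as withdrawing from the study, and collecting data is not the same as analysing them. Both statements can be true. What stands is that sections 2.3, 2.7 and 2.12, taken together, leave it unclear whether such participants count.
- **The activity criterion excludes the whole MAT group.** Taken literally it would, since MAT adds two 50-minute sessions a week. Section 2.4 shows that training other than MAT is meant. What stands is loose wording: section 2.3 does not say so.
- **Collected data are thrown away for good.** No section says this. Section 2.3 does not even say that excluded participants leave the analysis; that is inferred from where the rule sits. Details of analysis sets may also lie in a plan that is not shown. The finding concerns the rule the article does state.
- **DBS change as a response to MAT.** This is implausible within 12 weeks.
- **The worst-case figures as the expected bias.** They assume that removal follows outcome perfectly and in one arm only. With 16 per arm and the single worst changer lost from each, bias is about zero, false positives are 6.6% and power is 0.88.

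It is also fair to say that there is no randomised comparison here to break, and that keeping everyone in will not remove the confounding from preference. Finally, some would prefer an estimate under stable medication. That is a legitimate question, but dropping participants according to what happened to them does not answer it without bias.

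**Conclusion.** The point holds as a fault in the stated eligibility rule, and it should be fixed. Medication change, activity change and withdrawal are post-entry events that can depend on group and symptom course. Using them as exclusions adds selection to existing confounding.

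The size is uncertain, because the article gives no rate for these events and no link between them and outcome. With 2 to 3 of 15 lost from one arm, the distortion runs from about 0.10 SD under partial selection to 0.29 SD in the worst case, against a design effect of 1.0 SD. The false-positive rate goes from a nominal 5% to between 6% and 16%, or power from 0.84 to between 0.74 and 0.57. These figures rest on the assumed correlation of 0.6, normal change scores and one-sided loss. If losses are few or balanced between groups, the bias is small.

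**What to change.** 1. In section 2.3, keep only criteria that are known before allocation.
2. Move medication, DBS and activity changes and withdrawal to a list of events recorded during the study. State that activity change refers to training other than MAT.
3. Assess everyone allocated at 12 weeks where consent permits, and analyse them in their allocated group with all available data.
4. Report the analysis without participants who had such events as a sensitivity analysis.
5. Reconcile sections 2.3, 2.7 and 2.12 in one sentence saying whether those who interrupt or withdraw count in the comparison.

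The cost is an amendment to the eligibility text and one extra analysis; the planned sample size does not change. The small downside is that the main estimate will include some participants whose medication changed, and the sensitivity analysis shows how much that matters.
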